**1.2 Introduction**

In December 2019, a new coronavirus, SARS-CoV-2, caused an international outbreak of the respiratory disease COVID-19. The virus rapidly spread around the world, with nowadays cases in Asia, Europa, the United States, and Africa. The spectrum of COVID-19 ranges from mild, self-limiting respiratory tract illness to severe progressive pneumonia, ARDS, pulmonary oedema, multi-organ failure and eventually death.^1-4^ This has led to a tremendous increase of hospital admissions all over the world.

It is known that survivors of critical illness can develop several physical, cognitive and psychological impairments due to their treatment on the Intensive Care Unit (ICU), referred to as the post-intensive care syndrome (PICS), negatively affecting the health-related quality of life and the ability to return to work (HRQoL).^5-8^ In addition, patients admitted to the hospital after unintentional injury, cardiac disease and traumatic brain injury are also at risk for developing posttraumatic stress disorder (PTSD), anxiety and depression, also negatively impacting the HRQoL and ability to return to work.^9-17^ The SARS-CoV-2 outbreak came unexpected, with many patients admitted to the hospital in exceptional conditions. It can therefore be expected that patients admitted to the hospital during the COVID-19 pandemic are at risk for developing psychological impairments, such as PTSD, anxiety and depression, and a decreased functional ability, quality of life and ability to return to their former life.

In the current study, we therefore aim to examine the psychological burden in patients admitted to the hospital with symptoms suggestive of COVID-19 and examine the HRQoL.

**1.2.1 Objectives**

The primary objective is to quantify the psychological burden and the effect on health-related quality of life (HRQoL) of hospitalization during the pandemic, in terms of anxiety, depression and post-traumatic stress disorder, 1 month, 3 months and 12 months after discharge. Secondary objectives are 1) to examine possible differences between COVID-19 and non-COVID-19 patients and 2) to examine possible differences between COVID-19 ICU patients and COVID-19 non-ICU patients.

**1.2.2. Trial Design**

This study is designed as a single center, observational, prospective cohort study.

**1.3 Methods: participants, measures, and outcomes**

**1.3.1 Study setting**

This study will be carried out in the Franciscus Gasthuis & Vlietland hospital, a hospital providing secondary care in Rotterdam, the Netherlands between April 2020 and July 2021.

**1.3.2 Eligibility criteria**

Adults (≥ 18 years old) admitted to the Franciscus Gasthuis & Vlietland hospital between 16th of March 2020 and 28th of April 2020, with symptoms suggestive of COVID-19 and fluent in the Dutch language were eligible for inclusion. Symptoms suggestive of COVID-19 is defined as the presence of respiratory symptoms (e.g. dyspnea, coughing, sore throat, rhinorrhea, saturation <94% or respiratory rate >24/minute), and/or gastro-intestinal symptoms (e.g. diarrhea or vomiting), for a duration of more than 24 hours. Patients had to be subsequently tested for SARS-CoV2 with PCR.

**1.3.3 Exclusion criteria**

Patients were excluded when they already participated in other interventional studies or when their formal house address or e-mail address was unknown.

**1.3.4 Participants timeline**

All patients admitted to the hospital with a suspicion of COVID-19 are registered in the International Severe Acute Respiratory and emergency Infection Consortium (ISARIC, Oxford, United Kingdom) and Castor EDC (Castor EDC, Amsterdam, the Netherlands). Eligible patients are approached 1 month after discharge from the hospital by sending an information letter explaining the nature and aim of the study accompanied by the first set of questionnaires. Participation in the questionnaire takes approximately 15 minutes. Since participation requires only a limited amount of effort and time, the standardized informant-consent procedure was simplified. At the beginning of the questionnaire, patients are asked for consent to use the data gathered using the questionnaires. Patients who agree to participate receive the second set of questionnaires 3 months and 12 months after hospital discharge by e-mail or postal mail, depending on the stated preference. Patients who do not want to participate are asked to return the questionnaire empty. All non-responders are called two weeks after sending the questionnaire as a reminder. Non-responders unable to be reached by telephone are send the second and third questionnaire. Patients who deny participation either via telephone or by returning an empty questionnaire, are excluded from further follow-up.

Data gathered using the questionnaires will be anonymized and will not have an influence on the standard hospital care of these patients in any way possible.

**1.3.5 Sample size**

Due to the nature of the study design and the lack of previous data regarding psychological outcome after COVID-19, we were unable to calculate an a prior sample size.

**1.4 Methods: data collection, management, analysis**

**1.4.1 Data collection Methods**

All data will be collected using electronic data capture system Castor EDC (Castor EDC, Amsterdam, the Netherlands) and International Severe Acute Respiratory and emergency Infection Consortium (ISARIC, Oxford, United Kingdom).

Demographic and treatment related characteristics will be retrieved from patients records and include age, gender, ethnicity, BMI, employment as healthcare worker, medical history, hospital length of stay, ICU admission, ICU length of stay, diagnosis COVID-19; SOFA score, P/F ratio and S/F ratio at first day of COVID-19 suspicion; need and duration of oxygen therapy, non-invasive ventilation, invasive ventilation and prone positioning and insertion of tracheostomy. Educational level, employment status and the psychiatric history will be additionally assessed using a self-composed questionnaire.

Symptoms of PTSD are assessed using the Impact of Event Scale – Revised (IES-R). The IES-R is a validated 22-item questionnaire and assesses subjective distress caused by a traumatic event. The IES-R yields a total score (ranging from 0 to 88, higher scores indicating more severe symptoms) and subscale scores can be calculated for symptoms of intrusion, avoidance, and hyperarousal. A total IES-r score above 24 is classified as clinically significant symptoms of PTSD.^18,19^

Symptoms of depression and anxiety are assessed using the Hospital Anxiety and Depression Scale (HADS). The HADS is commonly used to determine the levels of anxiety and depression that a person is experiencing. The HADS is 14-item scale that generated ordinal data. Seven of the items relate to anxiety and seven relate to depression. The HADS yields a depression and anxiety sum score, ranging from 0 to 21 with higher scores indicating more severe symptoms. A sum score above 8 of either the depression or anxiety subscale is classified as clinically significant symptoms of depression or anxiety.^20,21^

HRQoL is assessed using the European Quality of Life 5-dimensions-5-levels (EQ-5D-5L/EQ-5D) questionnaire and the RAND-36. The EQ-5D measures the HRQoL on five dimensions (mobility, self-care, usual activities, pain/discomfort and anxiety/depression), by which the weight of a health state can be computed, ranging from -0.446 (worst quality of life) to 1.000 (best quality of life). Additionally, patients score their current subjective health state on a visual analogue scale (the EQ-VAS), ranging from 0 (worst health imaginable) to 100 (best health imaginable).^22,23^ The RAND-36 is 36-item, patient reported survey of patient’s health. The RAND-36 yields eight scaled scores, which are weighted sums of the questions in their section. Each scale is directly transformed to a 0-100 scale on the assumption that each question carries equal weight. The scales are vitality, physical functioning, bodily pain, general health perceptions, physical role functioning, social role functioning and mental health.^24,25^

**1.4.2 Data Management**

All data collected during the study will be entered digitally in the electronic data capture system Castor EDC (Castor, Amsterdam, the Netherlands) and the International Severe Acute Respiratory and emergency Infection Consortium (ISARIC, Oxford, United Kingdom). Checks will be applied at the time of data entry into a specific field and/or before the data is written (committed) to the database. Modifications to data written to the database will be documented through the data change system. Data entered into the database will be retrievable for viewing through the data entry applications. All patients are assigned to a unique study identification number and all data will be analyzed anonymously. Original study forms, such as filled in questionnaire, will be stored at each study site in a secured location and will be kept for a minimum of 15 years.

**1.4.3 Statistical Methods**

Baseline demographics will be communicated using descriptive statistics. Continuous variables will be presented as mean (SD) when normally distributed and as median (IQR) when not normally distributed. Categorical variables will be presented as absolute number and relative frequency.

Patients will be stratified based on the confirmation of the diagnosis COVID-19 and, within the COVID-19 patients, on necessity for ICU treatment. Differences between stratifications will be analyzed using a Standard Student’s T-test if the residuals are normally distributed or using a Mann-Whitney U test when the residuals are not normally distributed. Differences in categorical variables will be analyzed using a Chi-squared test or, in case of small sample sizes, a Fisher’s exact test.

Missing data will not be imputed due to the observational nature of the study.

All analyses will be performed using SPSS (version 24.0; SPSS Inc., Chicago, IL) and R for Statistics (R Foundation for Statistical Computing, Vienna, Austria, 2015). A P-value ≤0.05 will be considered statistically significant.

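### Both secondary group contrasts in this observational cohort are planned with unadjusted tests only, which describe a difference but cannot support attributing it to COVID-19 or ICU treatment

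*Protocol*

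**What the plan says.** Section 1.2.2 describes the design: "This study is designed as a single center, observational, prospective cohort study". Section 1.2.1 sets two between-group secondary objectives: "to examine possible differences between COVID-19 and non-COVID-19 patients" and "to examine possible differences between COVID-19 ICU patients and COVID-19 non-ICU patients".

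Section 1.4.3 forms the groups and names the tests. "Patients will be stratified based on the confirmation of the diagnosis COVID-19 and, within the COVID-19 patients, on necessity for ICU treatment". Then "Differences between stratifications will be analyzed using a Standard Student’s T-test" if residuals are normal, or "using a Mann-Whitney U test when the residuals are not normally distributed". For the rest: "Differences in categorical variables will be analyzed using a Chi-squared test or, in case of small sample sizes, a Fisher’s exact test". The same section gives baseline variables a descriptive role, rules out imputation and sets significance at P ≤ 0.05.

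Section 1.4.1 lists, from patient records, age, gender, ethnicity, BMI, healthcare work and medical history, together with acute severity and treatment variables. It adds: "Educational level, employment status and the psychiatric history will be additionally assessed using a self-composed questionnaire".

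**The concern.** Whether a patient is PCR-positive or PCR-negative, or goes to ICU or stays on the ward, is not decided by chance. Under section 1.3.2 the non-COVID-19 group consists of people admitted with respiratory or gastro-intestinal symptoms whose test did not confirm COVID-19, so their illnesses are mixed. ICU patients are selected by need. Similar age, comorbidity and psychiatric history cannot be presumed in either contrast, and each can plausibly influence the IES-R, HADS, EQ-5D and RAND-36 results.

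The planned tests compare the groups as they stand. If the groups differ beforehand, a P-value below 0.05 may reflect that difference rather than COVID-19 or ICU care. The document makes a causal reading easy. Its introduction speaks of impairments arising from ICU treatment, and nothing in the plan warns against reading the contrasts in that way. The variables needed to address this are largely collected already, but they have no stated role in the comparisons.

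**Working it through.** **1. Text check.** The protocol states no sample size, power, effect size or SD (section 1.3.5 says that no sample size could be calculated), so it has no figure to reproduce. The check sets the objectives against the methods.

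- Contrasts to be answered: two, both non-randomised (sections 1.2.1 and 1.2.2).
- Procedures named for them: Student's t, Mann-Whitney U, chi-squared and Fisher's exact (section 1.4.3). None takes a covariate.
- Regression, matching, weighting or stratification on a confounder: not mentioned in any section.
- The word stratified in section 1.4.3 defines the comparison groups. It does not mean stratification on a confounder.
- Deferral to another document: none stated.

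**2. How large could the distortion be?** All inputs below are assumptions chosen to show a range. The true group effect is set to zero and the test is two-sided at 0.05 (the protocol does not state sidedness).

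*Score outcome.* Spurious difference d (in SD) = shift of the confounder between groups (in SD) × its correlation with the outcome. With SE = √(1/n₁ + 1/n₂), the rejection rate is Φ(d/SE − 1.96) + Φ(−d/SE − 1.96).

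Worked line: shift 0.5 and correlation 0.3 give d = 0.15. With 100 per group, SE = √(2/100) = 0.141 and d/SE = 1.06. The rate is 18.6%.

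*Cut-off outcome.* Spurious risk difference = difference in confounder prevalence × risk difference due to the confounder. With prevalence 20% vs 40% and risk 15% without and 40% with the confounder, the difference is 0.20 × 0.25 = 5 points. The group risks are 0.80 × 0.15 + 0.20 × 0.40 = 20% and 0.60 × 0.15 + 0.40 × 0.40 = 25%. The rejection rate uses the pooled variance for the test.

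| Assumed confounding (no true effect) | Spurious difference | 50 per group | 100 per group | 200 per group |
|---|---|---|---|---|
| No imbalance | 0 | 5% | 5% | 5% |
| Prevalence 20% vs 30%; risk 15% vs 30% | 1.5 points | 5.4% | 5.8% | 6.7% |
| Shift 0.25 SD × correlation 0.2 | 0.05 SD | 5.7% | 6.4% | 7.9% |
| Prevalence 20% vs 40%; risk 15% vs 40% | 5 points | 9.2% | 13.5% | 22.3% |
| Shift 0.5 SD × correlation 0.3 | 0.15 SD | 11.7% | 18.6% | 32.3% |
| Shift 1.0 SD × correlation 0.4 | 0.40 SD | 51.6% | 80.7% | 97.9% |

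Unequal groups, with an assumed d of 0.25 SD:

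- 50 vs 100: SE = √(1/50 + 1/100) = 0.173, and the rate is 30.3%.
- 25 vs 75: SE = √(1/25 + 1/75) = 0.231, and the rate is 19.1%.

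**3. Reading.** The distortion runs from negligible to dominant depending on inputs that the documents do not supply. The spurious difference itself does not shrink as n grows, so more patients make a false attribution more likely, not less. Several confounders may also act in opposite directions, so even the sign of the net bias is unknown.

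**4. Which collected variables are suitable?** Age, gender and medical history come from records and precede the exposure. Educational level and psychiatric history come from the patient questionnaire, and the first questionnaires go out one month after discharge (section 1.3.4). Education is unlikely to have changed by then. Psychiatric history must refer to the time before admission. Employment status has no stated reference time and could be a consequence of the illness. Length of stay, ventilation and tracheostomy lie on the pathway from exposure to outcome. SOFA score and P/F ratio on the first day of suspicion may be consequences of COVID-19 in the first contrast.

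**The case against.** The strongest reply is that the secondary objectives ask only whether groups differ. For that question the crude difference is the right quantity and the named tests have the matching null hypothesis. This stands. A reader might infer that the planned tests are invalid, biased or aimed at the wrong null. That would be so only if the contrasts were defined as effects of COVID-19 or of ICU treatment, and section 1.2.1 does not define them so. It uses the word effect in the primary objective, for hospitalisation in the whole cohort.

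A second reply is that a separate SAP, which was not available, might add adjusted models. Section 1.4.3 does not say that its tests are the only analyses. This has limited force, because the section names specific tests, leaves nothing open and refers to no further plan.

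A third reply is that adjustment has its own difficulties. Some covariates are self-reported after discharge. Models without imputation lose patients with any missing covariate. The ICU group may also be too small for many terms. This stands too, and it argues for a short covariate list rather than against adjustment. That questionnaire covariates exist only for responders adds little, because the outcomes also exist only for responders.

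**Conclusion.** The point holds in a limited form. For two non-randomised contrasts the protocol plans only tests that cannot adjust, while collecting likely confounders. The results will be usable as description. They may be confounded, and they cannot support a statement that COVID-19 or ICU treatment produced a difference.

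It would go too far to say that the contrasts will certainly be confounded, or by how much. The documents contain no imbalance, no covariate effect and no group size, and the 5.4% to 97.9% range rests wholly on assumed inputs. It would also go too far to treat this as a flaw in the study's main aim. Quantifying burden at 1, 3 and 12 months in the cohort does not depend on these contrasts. The change should be made before the analysis; it is not a condition for the study's primary result.

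**What to change.** Amend section 1.4.3 as follows.

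1. Keep the t, Mann-Whitney, chi-squared and Fisher tests, labelled as descriptive.
2. For both contrasts, add covariate-adjusted linear models for the scores and logistic models for the IES-R and HADS cut-offs.
3. Fix a short set of pre-admission covariates in advance: age, gender, medical history, psychiatric history before admission and educational level. Include employment status only if it is recorded as of before admission.
4. Exclude variables on the pathway: length of stay, ventilation and tracheostomy.
5. Limit the number of covariates to what the smaller group supports (for the logistic models, also the number of patients above the cut-off), and state the order in which covariates would be dropped.
6. State that unadjusted differences will not be interpreted as effects of COVID-19 or of ICU treatment. Add that the adjusted ICU contrast still mixes ICU treatment with acute severity, which pre-admission covariates do not capture.

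Cost: a paragraph of text and modest programming in software already named, with no new data unless the reference time of employment and psychiatric history needs clarifying. The price in the analysis is some degrees of freedom and, because missing data are not imputed, the loss of patients with a missing covariate. Report the number analysed in each model beside the crude comparison.

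### The test for scale scores is chosen by a normality check and names the standard Student t-test: 0.05 is not protected if group sizes and variances both differ, and the test can change between visits

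*Protocol*

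**What the plan says.** Protocol section 1.4.3 defines the groups: "Patients will be stratified based on the confirmation of the diagnosis COVID-19 and, within the COVID-19 patients, on necessity for ICU treatment". Continuous outcomes are then compared "using a Standard Student’s T-test if the residuals are normally distributed or using a Mann-Whitney U test when the residuals are not normally distributed", and "A P-value ≤0.05 will be considered statistically significant". No unequal-variance version of the t-test is mentioned. The section does not say whether the check is made once per outcome or again at each visit.

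The rule serves both secondary objectives in section 1.2.1, one of which is "to examine possible differences between COVID-19 ICU patients and COVID-19 non-ICU patients". Outcomes are measured "1 month, 3 months and 12 months after discharge". They include bounded scores: section 1.4.1 gives HADS subscales from 0 to 21, IES-R from 0 to 88, and EQ-VAS and RAND-36 scales from 0 to 100.

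On numbers, section 1.3.5 states that "we were unable to calculate an a prior sample size". No expected ICU share, group size or SD appears anywhere.

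**The concern.** There are two separate weaknesses.

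First, the check does not test the assumption that matters most when groups are unequal in size. The standard Student t-test pools the two variances. If the smaller group varies more, pooling understates the standard error and the test rejects too often; if it varies less, the test rejects too seldom. A residual normality check is not designed to detect this, and Mann-Whitney is not level-robust to unequal spread either. Group sizes here are not set by design. They follow from who was admitted between 16 March and 28 April 2020, who needed ICU care and who answered the questionnaires.

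Second, a test chosen from the observed residuals can differ between visits for the same scale. A mean comparison at 1 month and a rank comparison at 12 months test different hypotheses, so the two p-values cannot be read as a course over time.

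At stake is the interpretation of the between-group comparisons of scale scores.

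**Working it through.** **Inputs from the protocol.** The test rule and the 0.05 threshold (section 1.4.3); three visits (section 1.2.1); bounded scales (section 1.4.1). The threshold is the only error-rate figure stated, so there is no sample size or power figure to reproduce.

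**Assumptions.** Two-sided testing; Shapiro-Wilk on pooled residuals at 0.05 as the check (the protocol names none); group sizes and SD ratios as shown. The SD ratio r is the smaller group's SD divided by the larger group's. True means are equal throughout.

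**Step 1: large-sample size of the pooled t-test.**

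Size = 2 × [1 − Φ(1.96 × √(V_pooled / V_true))], where

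V_true = s1²/n1 + s2²/n2

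V_pooled = [((n1−1)s1² + (n2−1)s2²)/(n1+n2−2)] × (1/n1 + 1/n2)

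For 20 vs 80 and r = 1.5:
- V_true = 2.25/20 + 1/80 = 0.1250
- V_pooled = [(19×2.25 + 79)/98] × 0.0625 = 1.2423 × 0.0625 = 0.0776
- √(0.0776/0.1250) = 0.788; 1.96 × 0.788 = 1.545; size = 0.122

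The same formula gives 0.181 at r = 2 and 0.013 at r = 0.67. At r = 1 the two variances coincide and the size is 0.050. With 50 vs 50 and r = 1.5 they coincide again (1.625 × 0.04 = 0.065 and 3.25/50 = 0.065), so the size is 0.050.

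**Step 2: the whole rule, check included.** 8,000 simulated normal data sets per setting. The Monte Carlo standard error is √(0.05×0.95/8000) = 0.002 near 0.05 and √(0.12×0.88/8000) = 0.004 near 0.12.

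| Groups | r = 0.67 | r = 1 | r = 1.5 | r = 2 |
|---|---|---|---|---|
| 10 vs 50 | 0.010 | 0.050 | 0.133 | 0.193 |
| 15 vs 60 | 0.015 | 0.052 | 0.121 | 0.173 |
| 20 vs 80 | 0.017 | 0.052 | 0.116 | 0.161 |
| 20 vs 100 | 0.011 | 0.050 | 0.128 | 0.174 |
| 30 vs 90 | 0.020 | 0.047 | 0.103 | 0.131 |
| 50 vs 50 | 0.052 | 0.049 | 0.053 | 0.060 |

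In the unbalanced settings Mann-Whitney alone gives 0.078 to 0.090 at r = 1.5 and 0.094 to 0.116 at r = 2. Welch's t-test gives 0.046 to 0.054 in every setting of the table.

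**Step 3: skewed HADS-like scores (0 to 21, equal mean 5; 15 vs 60, 20 vs 80 and 30 vs 90).** The rule rejects in 0.051 to 0.052 with equal spread, 0.119 to 0.136 when the smaller group's SD is about 4.8 against 3.5, and 0.051 to 0.081 when these SDs are reversed. Welch gives 0.051 to 0.063. Part of the rule's excess is not false rejection in the strict sense, because Mann-Whitney does not test equality of means.

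**Step 4: change of test across three visits, with the distribution unchanged.** 2,000 runs per setting; the check is assumed to be made at each visit.

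| Assumed score | Groups | Visit correlation | Studies with a change of test |
|---|---|---|---|
| Mild skew, EQ-VAS-like | 10/30, 15/60, 20/80 | 0.6 | 39%, 63%, 65% |
| Near-symmetric, 0 to 100 | 10/30, 15/60, 20/80 | 0.6 | 19%, 37%, 48% |
| Strong skew, HADS-like | 10/30, 15/60, 20/80 | 0.6 | 52%, 4%, 0% |
| Moderate skew (rounded gamma, cap 21) | 15/35 | 0 and 0.6 | 67% and 59% |
| Same | 20/80 | 0 and 0.6 | 8% and 7% |
| Same | 25/100 | 0 and 0.6 | 1.5% and 1.8% |

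Changes are frequent where the check is undecided. They nearly vanish where it almost always gives the same answer.

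**The case against.** The strongest objection is that the error-rate problem needs two conditions the protocol does not document: unequal group sizes and unequal variances. That stands. A reader might infer that the p-values of the ICU comparison are wrong, or are too small. The document does not support this: with equal SDs the rule holds about 0.05 at every ratio tried, with equal groups it stays between 0.049 and 0.060, and if ICU patients vary less the rule is conservative.

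A reader might also take one high switching figure as typical. The same gamma score gives 67% at 15 vs 35 but under 2% at 25 vs 100, where Mann-Whitney is chosen at all three visits in about 98% of studies. In that last case Student's t is hardly ever used, so its error rates say little about that outcome. Only a range is defensible.

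Further, the normality criterion and the level at which it is applied may be set in an analysis plan that is not shown; their absence is not held against the protocol. The point rests on what section 1.4.3 does state, namely the standard t-test and a choice made from the residuals.

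The scope is limited too. Outcomes classified by the IES-R and HADS cut-offs go to chi-squared or Fisher tests and are untouched, and the primary objective is to quantify burden. It would also be too strong to say that no size of difference is available under Mann-Whitney, since section 1.4.3 provides medians and IQRs for non-normal variables; what it does not name is an effect estimate with an interval.

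Finally, a rank test is a reasonable choice for bounded, skewed scores. Reducing it to a sensitivity analysis would be partly a matter of preference, so that is not asked for.

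**Conclusion.** The point holds in conditional form. The stated rule does not protect the 0.05 level if the ICU and non-ICU groups differ in both size and variance. At an assumed 1:4 ratio with normal data, and with the check applied, the error is about 0.12 to 0.13 at an SD ratio of 1.5, about 0.16 to 0.17 at 2, and about 0.02 at 0.67. It is about 0.05 if either the SDs or the group sizes are equal. Whether an error arises, and in which direction, cannot be read from the protocol. The same condition applies to the comparison of COVID-19 with non-COVID-19 patients.

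The possibility of a change of test between visits needs no assumption about imbalance or variance, since nothing in section 1.4.3 fixes one test per outcome. How often it would happen does depend on assumptions, and ranges from almost never to about two thirds of simulated studies.

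The consequence is moderate, because these are secondary comparisons in an observational cohort. The correction is worth making because it costs almost nothing.

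**What to change.** In section 1.4.3, replace the standard Student t-test with Welch's unequal-variance t-test. Name one method per outcome in advance, use it at 1, 3 and 12 months, and do not let a normality check select it. The default would be the mean difference with a Welch or robust 95% confidence interval. For strongly skewed scores a rank test may be kept, provided it is chosen beforehand and used at every visit.

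This is a one-sentence change, and Welch's test is standard output in SPSS and R, which the protocol already names. If the variances are in fact equal, the loss of power is negligible, and the simulated level at equal SDs stays near 0.05 (0.048 to 0.052). Change of test between visits is then excluded by construction.

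### The 1-, 3- and 12-month outcomes have no method that links a patient's repeated questionnaires, so each time point rests on whoever responded

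*Protocol*

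**What the plan says.** - **Objective and design (Protocol 1.2.1, 1.2.2).** The primary objective is to quantify psychological burden and quality of life at "1 month, 3 months and 12 months after discharge". The design statement reads "This study is designed as a single center, observational, prospective cohort study".
- **Follow-up (1.3.4).** The same people are measured again: "Patients who agree to participate receive the second set of questionnaires 3 months and 12 months after hospital discharge". Patients can leave: "Patients who deny participation either via telephone or by returning an empty questionnaire, are excluded from further follow-up". Patients can also come in late: "Non-responders unable to be reached by telephone are send the second and third questionnaire".
- **Analysis (1.4.3).** The contrasts are between patients: "Patients will be stratified based on the confirmation of the diagnosis COVID-19 and, within the COVID-19 patients, on necessity for ICU treatment". Continuous outcomes get a Student t-test or, if residuals are not normal, a Mann-Whitney U test. For the rest, "Differences in categorical variables will be analyzed using a Chi-squared test or, in case of small sample sizes", Fisher's exact test. Imputation is excluded, and the reason given is that the study is observational.
- **Not in 1.4.3.** No paired test, time effect, group-by-time term or repeated-measures model is named. No rule says which responders count at each time point.

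**The concern.** The study collects up to three questionnaires per patient, yet the stated analysis would be the same if the three surveys had gone to three unrelated samples. The Protocol does not tie the time points to a common set of patients and does not model missing answers. Followed as written, the burden at 1, 3 and 12 months is therefore summarised in three sets of available responders.

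Whether someone returns a questionnaire on anxiety, depression or post-traumatic stress may well depend on how they feel. If it does, each estimate is shifted. If that dependence also changes between time points, readers will see a rise or fall that no patient experienced. A patient's answers at the other times carry information about a missing one, and the plan does not use it.

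**Working it through.** The Protocol gives no sample size, prevalence, response rate or within-patient correlation, so there is no stated figure to reproduce. All inputs below are assumptions, used only to show direction and possible size.

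**1. What the named tests cover**

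| Question | Method in 1.4.3 | Adequate? |
|---|---|---|
| COVID-19 vs non-COVID-19 at one time | t / Mann-Whitney / chi-squared / Fisher | Yes, different patients |
| ICU vs non-ICU at one time | same | Yes, different patients |
| Burden at each time, allowing for non-response | descriptive summary of responders | Not addressed |
| Change within patients; difference in change between groups | none | No method given |

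**2. Effect of selective response on a prevalence.** Let p be the true prevalence, unchanged over time, and let r_c and r_n be the response rates of cases and non-cases at month 12. Assume month-1 response is representative.

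Observed prevalence = p·r_c / [p·r_c + (1 − p)·r_n]

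- p = 20%, r_c = 40%, r_n = 60%: 0.2×0.4 / (0.2×0.4 + 0.8×0.6) = 0.08 / 0.56 = **14.3%**
- p = 30%, 60% and 80%: 0.18 / (0.18 + 0.56) = **24.3%**
- p = 30%, 50% and 80%: 0.15 / (0.15 + 0.56) = **21.1%**
- p = 30%, 80% and 60%: 0.24 / (0.24 + 0.42) = **36.4%**
- any p with r_c = r_n: no distortion

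The direction depends on who responds. On the odds scale, the observed odds equal the true odds times r_c/r_n. For the first line this is 0.25 × (0.4/0.6) = 0.167, which is again 14.3%. A spurious change between two time points therefore needs r_c/r_n to differ between them. If the ratio is the same at all three, each prevalence is biased but its apparent course over time is flat.

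**3. What linking the questionnaires recovers.** A simulation used 200,000 patients with mean score 6, SD 4, within-patient correlation 0.6 and no true change. Month-12 response depended on the month-1 score.

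| Dependence of response on month-1 score | Responding at month 12 | Mean of month-12 responders | Estimate using month-1 score |
|---|---|---|---|
| weaker | 70.2% | 5.65 | 5.99 |
| stronger | 67.9% | 5.35 | 5.99 |

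The responders' own month-1 means were 5.44 and 4.93. Carried through the correlation, these give 6 + 0.6×(5.44 − 6) = 5.66 and 6 + 0.6×(4.93 − 6) = 5.36, in line with the simulated means. The correction works here because non-response was made to depend on an observed score.

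**The case against.** The strongest reply is that section 1.4.3 does what it sets out to do. It applies its tests between strata, the strata contain different patients, and this matches the two secondary objectives. The primary objective asks to quantify burden at three times and states no hypothesis of change or of a group-by-time difference. A model for time could be specified in a statistical analysis plan that is not available here, and excluding imputation does not exclude a mixed model. Attrition is ordinary in cohorts, and late entry is stated only for non-responders whom the telephone call did not reach.

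Much of this stands, and it rules out three stronger readings:

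- **That independent-group tests will be run across time points.** No section says so.
- **That the standard errors are therefore wrong.** With within-patient correlations of 0.5 to 0.7, unpaired tests of change would overstate the standard error by 1/√(1 − 0.5) = 1.41 to 1/√(1 − 0.7) = 1.83. That describes an analysis the Protocol does not plan. It also assumes every patient is seen at both times, and it would make such a test conservative rather than falsely positive.
- **That nothing can be estimated validly.** The between-strata comparisons at a single time use suitable tests.

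The reply does not remove the remaining point. Section 1.4.3 is not silent: it names its tests and closes off imputation. Selective response distorts the descriptive estimates of the primary objective even if no test across time is ever made. The quoted sentence concerns categorical outcomes only, but the sentence before it places the scores in the same position.

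**Conclusion.** The point holds as a worthwhile improvement, not as an error that invalidates the planned comparisons. The plan names no method that uses the within-patient link, and its follow-up rules allow the responder set to lose and gain patients. The burden at 1, 3 and 12 months thus rests on available responders, and differences between those figures cannot be read as change in patients.

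The size is unknown from the Protocol. On assumed response rates, a constant 20% could show as 14.3%, and a constant 30% as anything from 21.1% to 36.4%. These figures assume representative response at month 1 and response at month 12 that depends on case status. If response is unrelated to symptoms, there is no distortion and the loss is only the unused pairing.

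**What to change.** Keep the between-strata tests and add to section 1.4.3 one likelihood-based repeated-measures model per outcome, with time (1, 3, 12 months), group and time × group, using every returned questionnaire, including those of late entrants:

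- **Scores:** a linear mixed model, with transformation or robust or bootstrap inference if residuals are not normal.
- **Cut-offs:** a mixed logistic model or a weighted GEE. Unweighted GEE does not in general repair dropout that depends on earlier responses.
- **Report:** estimated means or prevalences at each time, change from month 1 and group differences, all with 95% confidence intervals.
- **Responders:** the number at each time and how many are common to each pair of times and to all three.

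The cost is wording and some programming in SPSS or R, both already named. No new data are needed and the rule against imputation is respected. The downside is a missing-at-random assumption: the model reduces bias from non-response related to observed scores but not from non-response driven by unobserved ones. Patients who never return a questionnaire contribute nothing to it, and late entrants have no month-1 score.
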